**Methods:**

In total, *N* = 192 healthy, adult participants will be assigned to six experimental conditions in a randomized order (one single-task, three dual-task (two in parallel and one as interruption), one multitasking, and one passive control condition). Salivary alpha-amylase as well as heart rate as markers for Sympathetic Nervous System Activity, heart rate variability as measure for Parasympathetic Nervous System (PNS) activity, and cortisol as measure for activity of the hypothalamic-pituitary adrenal (HPA) axis will be assessed at six time points throughout the experimental session. Furthermore, inflammatory markers (i.e., IL-6, C-reactive protein (CRP), and secretory immunoglobulin-A) will be assessed before and after the task as well as 24 hours after it (IL-6 and CRP only). Main outcomes will be the time course of these physiological stress markers. Reactivity of these measures will be compared between the experimental conditions (dual-tasking, work interruptions, and multitasking) with the control conditions (single-tasking and passive control).

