### Participants

In total, *N* = 192 (32 per condition) healthy, German-speaking adults between 18 and 40 years will be recruited. Exclusion criteria are diagnosed physical or psychological disorders (operationalized as diagnosed within the last 2 years), regular medication intake (exception oral contraceptives), pregnancy, a BMI ≥ 35 kg/m^2^, regular smoking (more than 5 cigarettes per week), or being an employee of the Friedrich-Alexander University Erlangen-Nürnberg (FAU). The latter is a requirement from the workers’ council of the FAU.

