### Power analysis

An a-priori power analysis has been conducted using G*Power (version 3.1.9.6). We expect to find small, but relevant effects and therefore used an effect size of *f* = 0.14 for power calculation (*f*^2^ = 0.02). We intend to achieve a power of 1 – β = 0.95 and used a Bonferroni-adjusted α-level of α_adjusted_ = 0.05/3 = 0.017 (see data preparation and statistical analysis). With these parameters a total sample size of *N* = 174 (29 per condition) is needed for an analysis of variance for repeated measurements (rmANOVA) with six measurement time points and six conditions. Based on our experience with similar studies, we expect a small drop-out rate of about 10% due to insufficient saliva or blood volumes and will, therefore, recruit additional 18 participants (3 per condition). This results in a total sample size of *N* = 192.

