### Hypotheses

#### Main hypotheses

With regard to the specificity hypothesis [45,46], we expect that pure digital stressors will trigger physiological responses of the SNS (i.e., an up-regulation), PNS (i.e., a down-regulation), as well as an activation of the immune system, but not of the HPA axis (due to the absence of a social-evaluative component). An additional activation of the HPA axis (i.e., an increase of cortisol levels) is expected for the conditions 5 and 6 (non-digital parallel dual-tasking and multitasking), in which we included a social-evaluative component by the presence of an experimenter.

Our main hypotheses, that are associated with research questions 1, 2, and 3 are:

Conditions 3 and 4 (digital work interruptions and digital parallel dual-tasking) will trigger responses of the SNS, PNS, and the immune system that are stronger than in the passive control condition 1 and the single-task control condition 2. No HPA axis response are expected for conditions 3 and 4.Conditions 5 and 6 (non-digital parallel dual-tasking and multitasking) will trigger responses of the SNS, PNS, HPA axis, and the immune system that are stronger than in the passive control condition 1 and the single-task control condition 2.

Regarding the time course of the physiological responses (if any will be found), we hypothesize fast responses of the SNS and PNS with a maximum immediately after the tasks. The HPA axis response is expected to be delayed with a maximum 20 minutes after the tasks. Slower responses are expected for the immune system with a maximum of 90 minutes after the task for IL-6 and s-IgA and 24 hours after the experimental session for CRP.

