### Data preparation and statistical analysis

For statistical analysis, IBM SPSS Statistics (version 26 or higher for Windows) will be used. Data will be screened for outliers, and outliers which differ more than 3 standard deviations from the participants’ mean will be excluded from further analysis. Test of normality will be conducted by means of the Kolmogorov-Smirnov test. If necessary, data will be transformed (e.g., by means of the natural logarithm or square root transformation) to achieve a normality distribution.

For main hypotheses testing (research questions 1, 2, and 3), rmANOVAs will be conducted. In the analyses, the between-subjects factor ‘Condition’ (with six levels, see above) as well as the within-subjects factor ‘Time’ (with either six levels (for sAA, cortisol, and ECG measures), two for CRP and IL-6, and two for s-IgA) will be included. Three separate analyses will be conducted, one for SNS and PNS markers (i.e., sAA, HR, and RMSSD) and six measurement time points (s_1_ to s_6_), one for cortisol as the only HPA-axis marker with the same six time points, and one for the immune parameters (i.e., IL-6, CRP, and s-IgA) and two measurement time points. An additional factor ‘Measure’ (e.g., with the levels IL-6, CRP, and s-IgA for immune parameters) will be included if necessary. A Bonferroni-adjusted α-level of α_adjusted_ = 0.05/3 = 0.017 will be used for the main analyses, because three separate rmANOVAs will be conducted. The potential confounders age, sex, BMI, use of oral contraceptives and menstrual cycle phase for female participants, as well as time of day will be included in all statistical analyses as covariates.

Research question 4 (i.e., perceived stress, state anxiety, and affect) will be investigated analogously to research questions 1 to 3 by means of a further rmANOVA. The same α_adjusted_ = 0.017 as for main hypothesis testing will be used. For analysis of research question 5 (i.e., associations with person characteristics and psychological variables), nominal scaled variables (e.g., sex and education) will be included as additional factors in further rmANOVAs. For metric variables, multivariate regression analyses will be conducted in which the potential moderator variables will be included as moderator variables. For these analyses, the SPSS macro PROCESS [102] will be used. For these analyses which refer to research question 5, an adjusted α-level of α_adjusted_ = 0.001 will be used.

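### The plan does not say that covariates are centred; if they enter the SPSS rmANOVA uncentred, the Time and Measure x Time tests refer to age 0, BMI 0 and hour 0 (Condition x Time is unaffected)

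*Protocol article*

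**What the plan says.** In Data preparation and statistical analysis, the protocol article states that "IBM SPSS Statistics (version 26 or higher for Windows) will be used" and that "For main hypotheses testing (research questions 1, 2, and 3), rmANOVAs will be conducted". The factors are Condition (six levels, between subjects) and Time (within subjects; six levels for sAA, cortisol and the ECG measures), with a factor Measure added if necessary. Age, sex, BMI, oral contraceptive use, menstrual cycle phase and time of day are the covariates; these "as well as time of day will be included in all statistical analyses as covariates". Research question 4 is handled in the same way. The preparation steps listed are outlier exclusion, a normality test and transformation. Centring and coding of covariates are not mentioned.

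The time course matters to the plan. The abstract says: "Main outcomes will be the time course of these physiological stress markers". Main hypotheses gives an expected peak time for each system, beginning: "Regarding the time course of the physiological responses (if any will be found), we hypothesize fast responses of the SNS and PNS". The hypotheses themselves, however, compare conditions: responses are expected "that are stronger than in the passive control condition 1 and the single-task control condition 2". On the sample, "healthy, German-speaking adults between 18 and 40 years will be recruited".

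**The concern.** In a repeated-measures general linear model, each covariate also receives a covariate x Time term. The Time test is then a test of the intercepts of the within-subject contrasts, that is, of mean change when every covariate equals zero. For uncentred age, BMI and clock time, this is an extrapolation to a person who cannot exist in this sample. SPSS uses covariates as supplied for these F tests, so following the section literally, with no centring step, gives that test.

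Two errors could follow in the Time and Measure x Time rows. A real course shared by the conditions could be reported as no effect of time, even beside adjusted means, evaluated at the covariate means, that plainly move. Conversely, a course that is flat on average could be reported as significant because its slope on age, BMI or time of day differs between time points. The same rows appear in the research question 4 model for perceived stress, anxiety and affect.

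**Working it through.** **1. What the sample size rests on.** Inputs from Power analysis: f = 0.14 ("therefore used an effect size of *f* = 0.14 for power calculation"), alpha = 0.017, power 0.95, six conditions, six time points. Assumed, because not stated: correlation 0.5 between time points, and sphericity. For the interaction, lambda = f^2 x N x m/(1 - rho) = 0.0196 x 174 x 6/0.5 = 40.92, with df 5 x 5 = 25 and (174 - 6) x 5 = 840. Power is 0.955 at N = 174 and 0.945 at N = 168, so in multiples of six the stated 174 is reproduced. The same inputs give 108 for a Time main effect and 720 for a Condition main effect. The 174 therefore fits Condition x Time.

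**2. What the Time test refers to.** For each of the five orthonormal time contrasts, z = a + condition effects + sum(b_j x_j) + error. Time tests a = 0. With centred covariates the intercept becomes a + sum(b_j mean_j), the change for the average participant. The condition coefficients do not change.

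**3. Loss of precision.** With covariates roughly uncorrelated, the variance of the uncentred intercept is that of the centred one times 1 + sum((mean_j/SD_j)^2). Assumed, because the documents give no distributions:
- age 26 (SD 5): 5.2^2 = 27.04
- BMI 23 (SD 3): 7.667^2 = 58.78
- time of day uniform from 10 to 18 h (mean 14, SD 8/sqrt(12) = 2.31): 6.06^2 = 36.75
- sex coded 0/1, half each: 1

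The factor is 1 + 27.04 + 58.78 + 36.75 + 1 = 124.6, so the standard error is about 11.2 times larger. Simulation gave 0.89 against 0.076, about 11.7 times.

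**4. Power of the Time test** (df 5 and (174 - 10) x 5 = 820, alpha = 0.05/3).
- Shared peak of 0.3 SD at one of six time points: the mean squared deviation is 0.09 x 5/36 = 0.0125, so lambda = 0.0125 x 174 x 6/0.5 = 26.1 and power is 0.97 centred. Uncentred, lambda = 26.1/124.6 = 0.21 and power is 0.02. Simulations gave 0.95-0.98 against 0.02.
- Shared peak of 0.8 SD: lambda is 185.6 centred (power 1.00) and 1.49 uncentred (power 0.05). Simulation gave 1.00 against 0.05-0.06.
- The plan's own f = 0.14, with other assumed covariates (age 25, SD 5; BMI 23.5, SD 3.2; time of day uniform from 9 to 18 h; sex 0/1): simulation gave 99.9% against 2.0%.

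**5. False rejection.** Take no mean change at the covariate means, but a slope of beta SD per covariate SD at the peak. The uncentred intercept is then displaced by beta x sum(mean_j/SD_j).
- Time of day only (sum 6.06): beta = 0.10 gives lambda 0.86 and rejection of 0.04; beta = 0.20 gives lambda 3.42 and 0.13. Simulations gave 0.03-0.04 and 0.12-0.13.
- Age, BMI and time of day, slopes in the same direction (sum 5.2 + 7.667 + 6.06 = 18.93): beta = 0.10 gives lambda 8.34 and 0.41; beta = 0.15 gives lambda 18.8 and 0.86. Simulations gave 0.36-0.39 and 0.82-0.85.
- Time of day only, with the slope scaled to its root mean square over the six time points (a larger slope at the peak), under the second covariate set: simulation gave 0.19 at 0.1 and 0.86 at 0.2.

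Centred, rejection stayed between 0.015 and 0.027 in these simulations, against the nominal 0.017.

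**6. Condition x Time.** In the f = 0.14 simulation, power was 95.1% under either coding. In every scenario of that simulation set the F statistics agreed to about 1e-14.

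**The case against.** The strongest reply is that the article nowhere says the covariates are entered raw, and that centring is a syntax detail which an article may leave to a fuller plan. The first part stands: a reader might infer that the plan prescribes raw covariates, but the text is silent. The point is therefore conditional on how the models are run. It is still worth making, because the section lists its preparation steps without centring and the software does not supply it.

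A second reply is that the Time main effect is not a hypothesis of this study. This also stands. A reader might take the abstract's emphasis on time course to mean that a null of no change over time is being tested. No such null is stated: research questions 1 and 2 and both main hypotheses compare conditions with controls, and the sample size fits that interaction.

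Nor is the Time row the only check that the tasks moved a marker. A drift shared with the passive video condition is no evidence of a task response; Condition x Time provides that evidence. Finally, an omnibus Time test pooled over six conditions cannot locate a peak, however the covariates are coded, so centring does not turn it into a test of the predicted peak times.

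**Conclusion.** The point holds as a minor one, limited to the Time and Measure x Time tests in the main and research question 4 models. If covariates are uncentred, those tests address a person outside the sample. The power loss, to about 0.02 for a 0.3 SD shared peak, appears under both sets of covariate assumptions, because the means of age, BMI and clock time lie many SDs from zero. The false-rejection rate is much less certain. It needs slopes that change over time, and it runs from about 3% to over 80% with their assumed size, direction and number. All figures also assume a correlation of 0.5, sphericity and N = 174.

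A reader might conclude that the main analysis or the sample size is broken. The documents do not support that: Condition x Time is exactly invariant to centring as long as no Condition-by-covariate term is fitted, and the main analysis names none. No between-condition conclusion changes.

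**What to change.** Add one sentence to Data preparation and statistical analysis: before every rmANOVA, age, BMI and time of day are centred at the mean of the sample analysed in that model, and sex and any other two-level covariate are centred or coded -0.5/+0.5. The Time and Measure x Time tests then refer to the average participant, and Condition x Time is left as it is.

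The cost is that sentence and a few lines of SPSS syntax. No new data are needed, and because analysis starts only after data collection ends, the change can be fixed beforehand.

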### Data management plan

To protect the participants’ privacy and to maintain confidentiality, all personal data is stored in password-protected files and secured against unauthorized access by third parties. The raw data and materials are only accessible to project-team members. Each participant is assigned a randomly generated code that does not allow any conclusions to be drawn about the person. Only this code is used for naming files and samples. Only completely anonymized data will be made available to other researchers after completion of the study or in data repositories. Only mean values and group statistics will be reported in publications.

### Dissemination and analysis plans

Data analyses will start after data collection is completed. Interim analyses are not planned. At least one paper will be submitted to a leading journal in the field. The pre-processed and anonymized data will be made publicly available at the Open Science Framework (OSF) after an Embargo period of about 5 years.

## Discussion

### Summary

Psychosocial stress and its immediate and long-term biological effects have been studied relatively well, but a link between psychobiological-oriented stress research and the effects of digital stress has largely been lacking. The aim of our study is to apply the methods of psychobiological stress research in the context of digital stress (i.e., the widespread phenomena multitasking and work interruptions), with the overarching goal to provide the foundations for a better understanding of the health effects of digital stress. We describe a study protocol of a comprehensive experiment that investigates effects of multitasking and work interruptions on physiological stress response patterns including SNS, PNS, HPA axis, and the immune system.

### Strengths of the planned study

So far, acute psychobiological stress response patterns have been well researched in the context of “classic” stress research for non-digital stressors. In contrast, psychobiological stress reaction patterns in the context of digital stress have hardly been studied so far [103]. The aim of the presented study is to bring digital stress from every day and working life into the laboratory context, and thus to make it experimentally investigable. Our experimental approach is the key strength of our study. It enables us to systematically induce multitasking demands or work interruptions and compare them with single-task and passive control conditions.

Moreover, our study will enable to differentiate between stress responses to pure digital stressors and stressors that also include a non-digital component (operationalized by the presence of an experimenter). Nevertheless, all active tasks–the digital and the non-digital ones–include a cognitive component and therefore our study design does not allow to differentiate between digital and cognitive stressors. However, this is not a restriction of our study with respect to our definition of digital stress as being related to the usage of digital technology and media, which is independent of the (e.g., mental) processes being involved.

### Potential risks

From a practical point of view, there is a risk that the blood and saliva volumes will be too low for analysis. However, this has been included in the sample size-calculation and will be minimized by training the experimenters by experienced researchers. A further potential risk is that the recruitment goal might not be fulfilled, e.g., due to the Covid-19 pandemic. In the case that another lockdown will be imposed, recruitment will be paused.

### Limitations

In our study, we will focus on multitasking and work interruptions as highly relevant modern stressors. Nevertheless, a variety of further digital stressors is conceivable [e.g., techno insecurity, techno overload, or techno invasion; 104]. Moreover, our operationalization of multitasking and work interruptions is just one of many possibilities and many more are possible.

A further limitation is that we cannot assess certain factors which might be related with the physiological stress response to multitasking and work interruptions. One of these are primary and secondary appraisal [105], which are known to be associated with acute stress responses in general. However, assessing them between the introduction of the task and the beginning of the task [e.g., by means of the Primary and Secondary Appraisal Scale; 106] would disrupt the procedure too much. A further and related factor which we cannot assess is executive functioning, of which especially attentional control has been shown to be related with HPA axis responses after acute stressors [107]. Furthermore, although we assess intelligence during some of the sub tasks, a comprehensive assessment [including emotional intelligence; 108] would be even more meaningful. A further potential limitation is the chosen passive control condition as we cannot rule out that watching the videos unintendedly leads to either stress induction or relaxation. However, the videos’ contents have been rated as being low arousing in previous studies [65,66]. Moreover, this task is better suited than other potential control tasks in which participants are instructed to do nothing at all, which are–in our opinion–more likely to induce relaxation and which are also much more difficult to control.

We will use a pragmatic age restriction of 40 years, because this has been shown to be suitable in previous studies from our group for recruiting healthy participants who do meet all inclusion criteria. Other age groups (older than 40 years as well as children and adolescents) would be interesting target groups for future follow-up studies. Besides, non-healthy participants with diseases which are known to be associated with stress reactivity or being associated with chronic stress development [e.g., depression or post-traumatic stress disorder, 109] should be subject of further investigations.

### Implications

Nevertheless–despite these limitations–, we deem that our study contributes to a deeper understanding on influences of stressors associated with the use of digital technology on humans’ health-outcomes. Specifically, our results are expected to expand our current knowledge base on the impact of multitasking and information load on humans’ psychobiological stress responses with particular focus on physiological response patterns. Stress exerts a strong influence on health via well-described processes [e.g., conceptualized in the Allostatic Load Model; 3,32,110]. In the long-term, stress is negatively associated with quality of life, health, and longevity of individuals and, thus, productivity of society [111,112]. Therefore, our study is of high relevancy.

Given the ubiquitous applications of digital technologies in modern workplaces and living environments, our findings will help to further understand the mechanisms between digital stressors in various occupational settings and adverse health outcomes [113]. Eventually, examination of job-related risks will inform policy and practice interventions in occupational health. Overall, the findings from our study will have important implications for better understanding the long-term health effects of the potential stressors multitasking and work interruptions in several settings.

## Conclusions

Our planned study will expand our understanding of the physiological response patterns due to the modern (digital) stressors multitasking and work interruptions. By quantifying objective parameters of biological stress responses and, thus, patho-physiologically relevant markers of digital stress, the health effects of digital stress will be made assessable. The findings will have important implications, especially in the context of health in digitalized working environments.
